### End of Study

The date on which the last participant completes the study post randomization and initiation of treatment as per the allocation into either interventional arm or control arm on Day 1.

**Final completion:** The end of study, is defined as the time when the last participant is assessed or participates in study procedures for evaluation in the study

### STUDY PROCEDURES:

Screening assessments and study procedures outlined in this section and in Table 1 can only be performed after obtaining a signed informed consent. This includes any discontinuation of the participant's medication for the purpose of participation in this study.

It is very important to attempt to perform study procedures and obtain samples at the precise time points stipulated below. When it is not possible to perform the study visit at the exact time point, the visit may be performed within the acceptable visit window as defined in the visit-specific section below.

All study procedures for a visit should be completed on the same day. Any missed visits, tests not done, or examinations that are not conducted must be reported as such on the CRFs. Subsequent study visits should resume on the original schedule. Missed assessments at prior visits should not be duplicated at subsequent visits.

#### Schedule of Assessments:

| Procedure                               | Screening visit | Baseline (Visit-1) (Day 1) | Day 28 (Visit-II) | Day 56 (Visit III) | Day 84 (Visit IV) | Day 112 (Visit V) Without medicine |
|-----------------------------------------|-----------------|----------------------------|-------------------|--------------------|-------------------|------------------------------------|
| Informed Consent                        | ✓               |                            |                   |                    |                   |                                    |
| Assessment of eligibility               | ✓               |                            |                   |                    |                   |                                    |
| Randomization                           | ✓               |                            |                   |                    |                   |                                    |
| Demographic data                        |                 | ✓                          |                   |                    |                   |                                    |
| History taking                          |                 | ✓                          |                   |                    |                   |                                    |
| Clinical examination, BP, Weight, waist |                 | ✓                          | ✓                 | ✓                  | ✓                 | ✓                                  |

|                                          |   |                           |   |   |   |   |
|------------------------------------------|---|---------------------------|---|---|---|---|
| circumference, BMI,                      |   |                           |   |   |   |   |
| Trial intervention                       |   | ✓                         | ✓ | ✓ | ✓ |   |
| ECG                                      | ✓ |                           |   |   |   | ✓ |
| TSH                                      |   |                           |   |   |   |   |
| HbA1C, Fasting Blood sugar               | ✓ |                           |   |   | ✓ |   |
| Hs-CRP, TNF- $\alpha$ & IL-6, HOMA-IR    |   | ✓                         |   |   | ✓ |   |
| Gut microbiota                           |   | ✓                         |   |   | ✓ |   |
| Lipid Profile                            | ✓ |                           | ✓ | ✓ | ✓ | ✓ |
| LFT, RFT, CBC                            | ✓ |                           |   |   | ✓ |   |
| Assessment criteria                      |   | ✓                         |   | ✓ | ✓ |   |
| Intervention compliance form (Diary log) |   | ✓ (issued to participant) | ✓ | ✓ | ✓ |   |

All visits, except baseline, may have a window period of  $\pm 5$  days, if the participant has any difficulty in visiting the

#### Clinical visits:

##### Baseline: Day 1

After the screening, the participants would be randomized and allocated into either of the two groups and the participant demographic details, drug history, medical history, surgical history and clinical assessment will be recorded in the CRF. The participant would be initiated into study and the intervention would be initiated as per the protocol. The general physician would prescribe the standard care as per the current guidelines after FRS assessment. The participant would be instructed to fill the therapy adherence regime in a diary log for every day till 84 days. Stool sample for gut microbiome assessment would be collected and sent for analysis.

The following procedures will be performed:

- Record concomitant medications, including statin (standard care), dose plus adherence for prior month
- Obtain body weight
- Record vital signs (blood pressure, heart rate, respiratory rate, and temperature);
- Collect fasting blood samples for Lipid profile, Blood sugar, Adiponectin, ghrelin, apolipoprotein A1 and apolipoprotein B, Hs-CRP, IL-6, LFT, RFT etc
- Collect stool sample for gut microbiome metagenomics analysis
- FRS

- Provide trial drug for 28 days

#### **Day 28, Day 56:**

The following procedures will be performed:

- Record concomitant medications, including statin (standard care) , dose plus adherence for prior month;
- Obtain body weight, BMI, Waist circumference
- Record vital signs (blood pressure, heart rate, respiratory rate, and temperature)
- Collect fasting blood samples for Lipid profile
- Provide trial drug for 28 days;
- Assess adverse events and compliance to the trial intervention for the past 28 days

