#### **Summary of trial design:**

Eligible patients will be randomized into either the TK group or the placebo group. After screening, a total of 5 visits will be scheduled at baseline (visit 1) and Day 28(visit 2), Day 56 (visit 3), and

Day 84 (visit 4) to assess treatment efficacy and safety and a final without medication follow-up on Day 112 (Visit 5) to assess the sustenance of the response obtained (if any) in the trial participants.

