#### **Day 84:**

The following procedures will be performed:

- Record concomitant medications, including statin (standard care) , dose plus adherence for prior month
- Obtain body weight
- Record vital signs (blood pressure, heart rate, respiratory rate, and temperature);
- Collect fasting blood samples for CBC, Lipid profile, Blood sugar, Adiponectin, ghrelin, apolipoprotein A1 and apolipoprotein B , Hs-CRP, IL-6, LFT, RFTetc
- Collect stool sample for gut microbiome metagenomics analysis
- FRS
- Provide trial drug for 28 days
- Assess adverse events and compliance to the trial intervention for the past 30 days

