### **Safety data collection, recording, and reporting:**

Clinical trials provide the evidentiary basis for regulatory approvals of safe and effective interventions. The safety of the trial intervention, will be evaluated by examining the occurrence of all adverse events and serious adverse events during the course of the study.

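### Adverse-event prompts look back a fixed 28 or 30 days, but the visit window allows gaps of up to 32 or 38 days, so some on-treatment days can go unprompted

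*Protocol*

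**What the plan says.** The Protocol's list for Day 28 and Day 56 instructs the site to "Assess adverse events and compliance to the trial intervention for the past 28 days". The list for Day 84 has the same item with a different period: "Assess adverse events and compliance to the trial intervention for the past 30 days". The list for Day 112 contains no adverse-event item.

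Under Schedule of Assessments, "All visits, except baseline, may have a window period of" plus or minus 5 days, where the participant has difficulty attending. The table has no adverse-event row. Under Study Procedures, after a displaced or missed visit, "Subsequent study visits should resume on the original schedule", and "Missed assessments at prior visits should not be duplicated at subsequent visits".

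The general rule, under Safety data collection, recording, and reporting, has no time limit: safety "will be evaluated by examining the occurrence of all adverse events and serious adverse events during the course of the study". The secondary outcomes list participant-reported AE/ADR in structured formats, also without a time limit. The daily diary described under Baseline is for therapy adherence; adverse events are not named as part of its content.

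**The concern.** The look-back fits the planned interval between visits but not the longest interval that the protocol permits. When the interval is longer, a site that follows the visit list literally asks about only its most recent part. The days left out are those just after the previous visit, when the participant has just been supplied with trial drug. In the first interval they are the first days of exposure.

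Safety is part of the primary objective, and participant-reported AE/ADR is the only adverse-event outcome listed. What participants report depends on what they are asked, and the visit lists hold the only explicit scheduled adverse-event prompts. An event that is never elicited cannot be recovered in the analysis. The use of 28 days at one visit and 30 at another, for nominal intervals of equal length, is also unexplained.

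**Working it through.** This is calendar arithmetic.

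**Inputs.** Nominal visit days are 1, 28, 56 and 84 (Summary of trial design). The window is 0 days at baseline and 5 days either way afterwards (Schedule of Assessments). The look-backs are 28, 28 and 30 days (lists for Day 28/Day 56 and Day 84).

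**Formulas.** Nominal gap = later nominal day − earlier nominal day. Longest gap = (later day + 5) − (earlier day − 5), with nothing subtracted at baseline. A look-back of L days from a visit on day v starts on day v − L, or on day v − L + 1 if the visit day counts as one of the L days. The unprompted days run from the day after the previous visit (from Day 1 itself in the first interval) to the day before the look-back starts. The two ways of counting give the ranges below.

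| Interval | Nominal gap | Longest gap | Look-back | Unprompted at worst |
|---|---|---|---|---|
| Baseline to Visit II | 28 − 1 = 27 | 33 − 1 = 32 | 28 | Days 1 to 4 or 5: 4–5 days |
| Visit II to III | 56 − 28 = 28 | 61 − 23 = 38 | 28 | Days 24 to 32 or 33: 9–10 days |
| Visit III to IV | 84 − 56 = 28 | 89 − 51 = 38 | 30 | Days 52 to 58 or 59: 7–8 days |

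**Nominal dates.** Gaps of 27, 28 and 28 days against look-backs of 28, 28 and 30 leave no unprompted day. The protocol's figures are consistent as long as visits fall on schedule.

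**Only one visit displaced.** If Visit II is on Day 23 and Visit III on Day 56, or Visit II on Day 28 and Visit III on Day 61, the gap is 33 days against 28, leaving 4–5 days. For Visit III to IV the same displacement gives 33 days against 30, leaving 2–3 days. If both visits are equally late (Day 33, then Day 61), the gap is 61 − 33 = 28 days and the second interval loses nothing.

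**Missed visit.** If Visit II is missed and Visit III is on time, the interval is 56 − 1 = 55 days. The 28-day question starts on Day 28 or 29, so Days 1 to 27 or 28 are unprompted. The rule against repeating missed assessments gives the site no instruction to fill that gap.

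**The case against.** The strongest reply is that nothing is actually excluded. The safety section covers all adverse events during the study, the AE/ADR outcome has no look-back, and onset dates are required. No passage tells a site to discard an event older than 28 or 30 days. This stands. A reader might infer that the uncovered days are lost to data collection, or that events are certainly undercounted, but the documents show only that those days fall outside the visit prompt.

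Second, the time phrase could belong to compliance alone, matching the 28-day supply. That reading is possible. But one verb and one period govern both items, so the adverse-event reading is the natural one, and the ambiguity itself needs removing.

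Third, the extremes need one visit five days early and the next five days late. The window is meant only for participants with difficulty attending, and the protocol stresses precise time points. This limits how often the worst case will occur, though smaller displacements also open a gap.

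Fourth, safety does not rest on recall alone: laboratory tests, ECG and vital signs are also scheduled. That is correct, but those measurements do not replace participant-reported events.

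Three further inferences are not supported:

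- The 38-day gap cannot involve the first doses. Baseline has no window, so that interval is at most 32 days.
- The compliance record is not broken, because the adherence diary is filled in every day to Day 84.
- Nothing in the protocol shows that late attenders are late because they are unwell.

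**Conclusion.** The point holds as an inconsistency between the visit-level prompts and the protocol's own rule on adverse events. The fixed look-backs of 28, 28 and 30 days are shorter than the longest permitted intervals of 32, 38 and 38 days. At worst about 4–5, 9–10 and 7–8 on-treatment days go unprompted, and 27–28 days if Visit II is missed and Visit III is on its nominal date.

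These figures assume that the period applies to adverse events as well as compliance, that sites follow the lists literally, and that visits fall at the edges of their windows. The protocol gives no basis for estimating how often that will happen.

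The consequence is a risk of under-recording. A reader might go further and infer a bias between arms. The documents do not support that: allocation is double-blind and the same prompts apply to both groups. The primary outcome is not affected. The correction is still worth making before data collection, because it costs almost nothing and events not asked about cannot be restored later.

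**What to change.** In the lists for Day 28/Day 56 and Day 84, replace the fixed periods with: *since the previous attended visit (since first dose at the first post-baseline visit)*. This closes the gap for displaced and missed visits alike and removes the unexplained difference between 28 and 30 days.

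Add an adverse-event row to the Schedule of Assessments, ticked at every post-baseline visit including Day 112, and add the matching item to the Day 112 list. Collection then runs without a break to the end of the study, as the safety section promises.

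The cost is wording in three visit lists, one table row and the corresponding CRF prompt. No visit is added, but the Day 112 visit gains an adverse-event question. Some participants will be asked to recall a slightly longer period, and a considerably longer one after a missed visit.

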#### **Day 84:**

The following procedures will be performed:

- Record concomitant medications, including statin (standard care) , dose plus adherence for prior month
- Obtain body weight
- Record vital signs (blood pressure, heart rate, respiratory rate, and temperature);
- Collect fasting blood samples for CBC, Lipid profile, Blood sugar, Adiponectin, ghrelin, apolipoprotein A1 and apolipoprotein B , Hs-CRP, IL-6, LFT, RFTetc
- Collect stool sample for gut microbiome metagenomics analysis
- FRS
- Provide trial drug for 28 days
- Assess adverse events and compliance to the trial intervention for the past 30 days

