**Intervention:**

**Group I :** Tablet Trikatu 1000 mg twice daily with luke warm water one hr after food for 12 weeks along with standard care (Statins)

**Group II:** Matching placebo 1000 mg twice daily with luke warm water one hr after food for 12 weeks along with standard care (Statins)

The participants in both groups will receive standard care as per the 2019 ACC/AHA

**Duration of intervention:** 12 weeks (84 days)

**Sample size:** 85 per group (Total 170)

**Study Population:** Patients with Dyslipidemia diagnosed based on the 2019 ACC/AHA Guideline on the Primary Prevention of Cardiovascular Disease.

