#### **Day 112:**

The following procedures will be performed:

- Record concomitant medications, including statin (standard care) , dose plus adherence for prior month
- Obtain body weight
- Record vital signs (blood pressure, heart rate, respiratory rate, and temperature);
- Collect fasting blood samples for Lipid profile

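### The Day 84 visit list hands out a fourth 28-day pack of trial drug, which conflicts with the 84-day treatment and the off-medication follow-up to Day 112

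*Protocol*

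**What the plan says.** The Protocol summary gives the duration of intervention as 84 days, and the Trial treatment section gives both groups 1000 mg twice daily for 12 weeks. Under Clinical visits, participants are told at baseline to "fill the therapy adherence regime in a diary log for every day till 84 days".

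The Summary of trial design then describes "a final without medication follow-up on Day 112 (Visit 5) to assess the sustenance of the response obtained". The Schedule of Assessments heads the last column "Day 112 (Visit V) Without medicine". A lipid profile is scheduled there and costed in the laboratory budget.

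The visit lists carry the dispensing instructions. A 28-day supply of trial drug is listed at baseline, in the shared list for Day 28 and Day 56, and once more at Day 84: "Provide trial drug for 28 days". The Day 112 list has no dispensing line.

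In the Schedule of Assessments, the trial intervention row is ticked at Day 1, Day 28, Day 56 and Day 84, and is blank at Day 112. The compliance-form row also ends at Day 84.

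**The concern.** Staff work from the visit lists, and the Day 84 list tells them to hand over a pack that the planned treatment does not need. The tick for trial intervention at Day 84 looks the same as the ticks at the three earlier dispensing visits. Someone checking the list against the table could therefore take it as confirmation.

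Two things are at stake. The first is exposure beyond the planned 12 weeks, in a period when the adherence diary and the compliance form have ended. The second is the meaning of the Day 112 lipid profile. Its stated purpose is to show whether a response persists once the product is stopped, and a sample taken during or just after a fourth pack cannot show that. If some participants take the pack and others do not, Day 112 mixes on-drug and off-drug values, with no diary to tell them apart.

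**Working it through.** **Inputs**
- Planned treatment: 12 weeks (Protocol summary; Trial treatment).
- Packs: 28 days each at Day 1, Day 28, Day 56 and Day 84 (visit lists).
- Dose: 1000 mg twice daily (Trial treatment).
- Trikatu group: 85 participants (Sample size).

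**The plan's own duration.** 12 x 7 = 84 days, which agrees with the stated 84 days.

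**Supply against need**

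| Visit | Days supplied | Running total | Nominal days covered |
|---|---|---|---|
| Day 1 | 28 | 28 | 1 to 28 |
| Day 28 | 28 | 56 | 29 to 56 |
| Day 56 | 28 | 84 | 57 to 84 |
| Day 84 | 28 | 112 | 85 to 112 |

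Three packs meet the need exactly: 3 x 28 = 84. With the fourth, supply is 4 x 28 = 112 days. The excess is 112 - 84 = 28 days, and 28/84 = 33%. Used back to back, the fourth pack runs to the nominal day of the visit that is meant to be off medication.

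**Size of the excess**
- Per participant: 28 days x 2 doses = 56 doses. At 1 g each this is 56 g of product.
- Upper bound for the Trikatu group, if nobody drops out and everyone takes the whole pack: 85 x 28 = 2,380 participant-days.
- Lower bound: 0, if staff do not hand out the pack or nobody takes it.

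**Does the visit window explain it?** The schedule says "All visits, except baseline, may have a window period of" ±5 days. A late Day 84 visit might leave a participant short before that visit. A pack handed over at the visit can only be used afterwards, so the window gives no reason for it.

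**Does a statin reading explain it?** If trial drug in these lists meant only atorvastatin, no line at any visit would dispense Trikatu or placebo. The same lists also refer to the statin separately, as standard care. A statin-only reading is therefore unlikely.

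**After the fix.** Without the Day 84 line, supply is 3 x 28 = 84 days, equal to the planned treatment, and no trial product is supplied for the follow-up interval.

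**The case against.** The strongest reply is that this is a line carried over from the earlier visit lists. The summary, treatment section, timeline, design description, diary instruction and the heading of the last schedule column all point to stopping at Day 84. Extra exposure would need staff to follow one line against all of these. That is a fair account of how the line arose, and it is why no expected amount of extra exposure can be given. It does not remove the instruction, which nothing else in the protocol withdraws.

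The second reply concerns wording. The budget has a row that labels atorvastatin as trial drug, so the term is not reserved for Trikatu and placebo. At Day 112 staff are also told to "Record concomitant medications, including statin (standard care) , dose plus adherence for prior month", so some statin supply after Day 84 would make sense. This stands in part. The term could cover both products, and the fix must not cut off the statin by accident. The budgeted 90 tablets per participant do not settle the matter. The figure matches neither 84 nor 112 days, and the cost is approximate and rounded.

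Some stronger conclusions are tempting, but the protocol does not support them:
- *That extra use would go wholly unrecorded.* It falls outside the diary and the compliance form, but the Concomitant Therapy section still requires every intervention to be recorded with its dose and its start and stop dates.
- *That the main result is compromised.* The primary outcome is LDL cholesterol from 0 to 12 weeks, taken at the Day 84 visit before a fourth pack could be used. None of the listed outcomes is defined at Day 112.
- *That an exact drug-free interval can be quoted for the plan as intended.* The ±5-day window applies to every visit after baseline, including Day 56, so the end of the third pack can itself shift.

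**Conclusion.** The contradiction is real and follows from the text alone. The visit lists supply 112 days of trial drug for an 84-day treatment, and the surplus 28 days fall on the interval defined as without medication.

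If the Day 84 line is followed, each participant may take up to 28 unplanned days of Trikatu or placebo. For the Trikatu group the ceiling is 2,380 participant-days. It assumes no attrition and full use of the pack, and it is not a forecast. The practical loss is that the Day 112 lipid value would no longer serve its stated purpose. The primary outcome and the listed secondary outcomes are unaffected.

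The conclusion assumes that trial drug in the visit lists includes Trikatu or placebo, which is the only reading under which those products are dispensed at all. That the final visit is off Trikatu or placebo but on the statin is a strong inference from the Day 112 list. The protocol does not say so outright. The point should be fixed, but it is a correction of wording and does not call the trial's main comparison into question.

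**What to change.** 1. Delete the dispensing line from the Day 84 list.
2. State under the Schedule of Assessments that Trikatu or placebo ends at Day 84, that the Day 84 tick for trial intervention marks the end of the course, and that the heading of the Day 112 column means off Trikatu or placebo.
3. Confirm that atorvastatin continues as standard care to Day 112. If it is to be dispensed at Day 84, name it in that list so that it cannot be confused with the trial product. The sponsor should also check its supply: one tablet daily to Day 112 needs 112 tablets, 112 - 90 = 22 more per participant than the budget line covers.

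The cost is a short wording amendment, with the sponsor and ethics committee approval that the protocol requires for important changes. It needs no extra visit, sample or participant. The only possible expense is the additional statin, if the trial is to supply it.
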